## Abstract

**Background:**

Military sexual trauma (MST) among veteran men is common, underreported, and associated with substantial psychological morbidity. Despite evidence that gender-related distress and shame pertaining to masculinity contribute to treatment avoidance and dropout, MST interventions within the US Department of Veterans Affairs have not been developed specifically for men.

**Objective:**

The objective of this study is to develop a gender-tailored group psychotherapy for veteran men with histories of MST. Guided by implementation science frameworks, the mixed methods study described in this paper proposes to iteratively refine the previously implemented Men’s MST Group (MMG), a 12-session, gender-tailored, trauma-focused group intervention that integrates dynamic group processes, mindfulness-informed distress tolerance, and psychoeducation.

**Methods:**

We draw on a synthesis of the intervention mapping framework and the access reconceptualization model to identify patient and system characteristics that contribute to treatment access and engagement. For aim 1, we will refine MMG through focus groups, qualitative interviews, and expert consultation. For aim 2, we will pilot-test MMG in a randomized controlled trial (n=32) comparing MMG to present-centered group therapy. For aim 3, we will evaluate implementation barriers and facilitators and iteratively refine the intervention through posttreatment qualitative interviews and expert panel review.

**Results:**

This study was funded with a start date of January 2025 and is anticipated to end in December 2029. As of July 2026, we have completed data collection for aim 1 and are currently analyzing data from 31 semistructured interviews. As of July 2026, we are also refining the MMG treatment protocol, which we plan to implement in a pilot randomized controlled trial in January 2027. Results of aim 1 are anticipated to be published in 2027. Participant recruitment for the aim 2 pilot trials has not begun.

**Conclusions:**

The goal of the current project is to refine and pilot-test a gender-tailored group psychotherapy for veteran men with histories of MST. We anticipate that the intervention will demonstrate feasibility, acceptability, and implementation potential because it was developed through an iterative process incorporating feedback from veterans, clinicians, and subject matter experts. Should study objectives be met, the next step will be to conduct a fully powered randomized controlled multisite trial. We additionally plan to disseminate findings regarding treatment needs, preferences, and barriers to care among men with histories of MST, which may inform future treatment development and implementation efforts beyond the current project.

## Introduction

### Background

Approximately 3.5% of veteran men and 44% of veteran women report a history of military sexual trauma (MST) [1]. Although women disproportionately experience MST, the absolute number of men who report MST (55,500 from 2004 to 2013) is relatively similar due to the larger proportion of men in the military [2,3]. Furthermore, MST likely remains vastly underreported among men, who experience multiple barriers to disclosure [4-7]. Men with histories of MST are also less likely to seek care compared to veteran women [2,6,8]. Thus, men with MST histories often wait decades to seek care for MST-related distress, contributing to pervasive life impairment [9-11]. While gender-based shame appears central to MST-related distress and treatment underuse, gender has often been overlooked in establishing evidence-based approaches, and to our knowledge, US Department of Veterans Affairs (VA) MST-related treatments have not been developed specifically for men [11].

To address this critical service gap, we drew on a time-limited, gender-tailored, and trauma-focused group therapy for men with histories of MST that was initially delivered as standard clinical care. The intervention (the Men’s MST Group; MMG) has been delivered for the past 7 years (2018-2025) and is designed to address the unique needs of this veteran population through promotion of agency, belongingness, and hope. Exploratory evaluation signaled strong retention as well as recovery and attitudinal shifts, including reductions in shame and posttraumatic stress disorder (PTSD) symptoms [12].

Rigorous research is needed to refine, test, and prepare for the implementation of this intervention. Moreover, given the fact that most men with histories of MST wait decades to seek treatment, research is needed to facilitate men’s use of MST-related services. In this research, guided by intervention mapping (IM) [13,14] and the access reconceptualization model (ARM) [15,16], we plan to iteratively refine the MMG intervention by interviewing veteran participants and mental health clinicians, conducting a pilot randomized controlled trial (RCT), and evaluating feasibility within the VA, with the long-term goal of national implementation. The goal of this paper is to describe the research protocol for this study.

### Men With Histories of MST: The Importance of Identity and Shame

MST is associated with transdiagnostic complexity and increased prevalence of PTSD and depression [17,18], substance use disorders [19], suicide [20,21], difficulty maintaining relationships and employment [2,3,22], and homelessness [23]. Men with histories of MST merit particular attention because core components of their distress may be underaddressed and undertreated. Research shows that men can often experience MST as an assault to masculine identity—holding erroneous beliefs that “if I had been more of a man I could have prevented the assault”—which can lead to profound ruptures in selfhood and avoidance [4,10]. Moreover, MST also has the potential to intersect with other aspects of one’s identity, including race, culture, and personal background—with perceptions that “they did this because of who I am”—thereby increasing one’s sense of shame [10,11].

In general, norms that define masculinity—stoicism, self-reliance, and suppression—are known to contribute to barriers to mental health treatment and recovery [24]. In the case of men’s MST, despite heightened distress, this population shows more pronounced patterns of treatment avoidance, underuse, and dropout. Male veterans with MST histories are no more likely to engage in mental health treatment than those without [8]. Moreover, male veterans use less MST-specific care than female veterans and are more likely to seek help for medical rather than psychiatric concerns [7]. Finally, while dropout rates from evidence-based practices, specifically prolonged exposure therapy (PE) and cognitive processing therapy (CPT) in VA settings, approach 40% for both men and women [25], individuals with MST as their focal trauma show difficulty participating in treatment [26].

Shame and treatment underuse mean that male survivors of MST often wait decades to seek care, potentially contributing to chronic and pervasive life impairment [7]. Persistent psychological distress and avoidance (which can be due to shame) also contribute to loss of agency and hopelessness [27-31]. As shown in Figure 1, MST can simultaneously lead to psychological distress, shame and avoidance, and hopelessness, all of which can cause life impairment. Thus, more research is needed to understand how identity-related distress and shame contribute to treatment avoidance among men with MST and develop and evaluate strategies that improve treatment engagement, retention, and recovery outcomes.

**Figure 1. F1:**
[figure not shown]
A model of untreated men’s military sexual trauma (MST). MDD: major depressive disorder; PTSD: posttraumatic stress disorder.

### Current Treatment Standards

Current treatment standards for addressing distress pertaining to men’s MST are based on limited research and adapted from trauma-focused studies and, thus, may not sufficiently address concerns about identity and shame.

CPT and PE are two first-line therapies for PTSD endorsed by the VA for addressing MST-related distress [32]. While there is support for the use of both CPT [33-35] and PE for men with MST histories [36,37], additional options for treatment may be necessary for a number of reasons. First, PTSD symptoms among veterans completing these treatments often remain above clinical cutoffs, and many patients recover to a degree that they no longer meet PTSD diagnostic criteria [38-40]. While this finding is not unique to CPT and PE, this suggests a need for treatment refinement and augmentation of existing trauma-focused treatments, including development of novel treatment approaches [37]. Second, CPT and PE also have high dropout rates. Approximately 38% to 40% of PE and CPT participants at the VA terminate treatment prior to completion, reflecting the difficulty of overcoming issues of engagement with treatment [25,26]. Thus, while dropout may be due to the nature of avoidance associated with both PTSD and trauma exposure, trauma-focused treatments may be particularly challenging for survivors of MST [6,8]. Third, these interventions are gender inclusive (not gender tailored) despite evidence that gender tailoring psychological interventions may be a useful strategy to enhance treatment engagement and outcomes [41]. Moreover, CPT and PE are trauma specific and not transdiagnostic; they assume a model where fear and anxiety are the core emotional components of MST-related distress, which can lead to underaddressing gender-based identity [42].

In addition to CPT and PE, two specialized group protocols have been promoted to address MST: Warrior Renew [43-45] and Courage Group [46]. Both are gender inclusive, which means that they are designed to offer relevant treatment to both men and women, can be delivered with mixed-gender cohorts, and promote group discussion that is likely significant to overcoming isolation and shame among male survivors of MST. However, because neither protocol is gender tailored specifically for men, more research is needed both for group MST-focused approaches and men’s MST treatment more generally.

### Gender-Tailored Group Psychotherapy: The MMG

Drawing on these observations, we propose to study an alternative treatment approach that is gender tailored, trauma informed, and transdiagnostic.

Group therapy is promising for several reasons. First, group therapy may be relevant for individuals with heightened shame and isolation who, in a group setting, may experience relief and belonging by being with peers with shared experiences [47-49]. Second, group therapy can rebuild masculine belongingness through mutual recognition and development of social support [50]. Third, group participation and orientation to helping fellow veterans has potential to leverage a military ethos of brotherhood and service [51].

The MMG is a trauma-focused and discussion-based group tailored to men with MST [9,12]. The group is informed by an acceptance-based and psychodynamic treatment framework that emphasizes mindful awareness of internal experience, affective tolerance, and the exploration of relational and intrapsychic meanings of trauma within a supportive group context. The group runs for 90 minutes and, with the exception of the first session, which serves to orient new cohorts, is structured with the following sequencing: (1) mindfulness practice (5-15 minutes); (2) open group discussion of a theme pertaining to MST recovery (30-45 minutes); (3) invitation for a group member to discuss an MST event, with encouragement to disclose emotionally laden memories of the trauma, followed by a dynamically oriented group discussion (30 minutes); and (4) coping skill practice (3 minutes).

A recent study of the MMG found initial evidence on its feasibility, acceptability, and clinical benefit [12]. Feasibility was reflected in high levels of engagement across the treatment pathway as over 80% of referred veterans attended at least one session and over 80% of those who began treatment remained until completion. Acceptability was reflected through qualitative data that showed that most patients described positive experiences of the group, including social connectedness, diminished shame, enhanced emotion regulation, greater engagement in treatment, and a renewed sense of hope. Clinical benefit was indicated through a medium–effect size change from before to after treatment in PTSD symptoms (Cohen *d*=0.666) and improved recovery (Cohen *d*=0.607) and a small–effect size change in shame and belongingness.

Given these initial findings, we propose to iteratively refine the MMG by interviewing veteran participants and mental health clinicians, conducting a pilot RCT, and evaluating feasibility within the VA.

## Methods

### Research Design

This protocol was developed and reported in accordance with the SPIRIT (Standard Protocol Items: Recommendations for Interventional Trials) 2025 guidelines [52]. The research design and methods used in this study are informed by a synthesis of the IM framework and the ARM to identify patient and system characteristics that contribute to treatment access and engagement. IM is a sequential, iterative framework for planning, developing, and implementing evidence-based interventions, where the completion of one IM step results in a product that is the guide for the subsequent step [53]. In Figure 2, research activities are guided by relevant IM steps 4 to 6 (with steps 1-3 already completed).

**Figure 2. F2:**
[figure not shown]
An intervention mapping (IM) approach to the Men’s Military Sexual Trauma (MST) Group (MMG). RCT: randomized controlled trial.

### Setting

The proposed study will be conducted at the mental health clinic of the VA Greater Los Angeles (VAGLA), where over 4000 unique veterans receive care annually. All interviews will be conducted via Microsoft Teams or in person in a private clinical office. Treatment will be conducted in person in a private VA clinical setting.

### Ethical Considerations

This protocol has been approved by the VAGLA Institutional Review Board (IRB). The trial is registered at ClinicalTrials.gov (NCT06741202). All study procedures will be conducted in accordance with the ethical standards of the IRB and applicable regulations.

### Aim 1: Treatment Refinement

#### Overview

To revise the MMG treatment protocol with attention to factors that support men’s access to and engagement and retention in mental health interventions (IM steps 4-5), we will pursue 3 subaims. For aim 1a, we will investigate factors related to men’s use of MST-related services by conducting semistructured qualitative interviews (n=24) with VA mental health clinicians, Vet Center clinicians, MST coordinators, and MST experts. Results from aim 1a will inform revision of the protocol. For aim 1b, we will review the revised protocol by convening 2 focus groups with the 2 most recent MMG cohorts (n=8). For aim 1c, we will convene a subset of aim 1a participants for an expert panel to finalize the MMG protocol.

#### Data Collection

For aim 1a, we will conduct individual 30- to 45-minute semistructured interviews virtually with clinicians and other experts. Participants will be asked about factors related to men’s mental health treatment engagement, including (1) strategies for promoting access and engaging and retaining male survivors of MST in VA-based treatment, (2) strategies for engaging male survivors of MST in a gender-tailored group therapy, (3) suggestions for improving MMG treatment components and group discussion topics, and (4) strategies for addressing gender and intersectional factors in psychotherapy for veteran men with MST histories. For aim 1b, we will conduct 2 virtual focus groups lasting approximately 60 minutes each and focus on MMG revisions. For aim 1c, we will conduct an MST expert panel comprising individuals (approximately 15) drawn from the 24 individuals who participated in aim 1a interviews and who expressed willingness to be on the expert panel. Operations partners will also be invited. Participants will be asked to advise on engagement strategies, MMG core components, and outcome measures. Subject matter expert diversity will be achieved through invitations to participate based on representation of clinician types [54].

#### Analysis

Data will be analyzed using rapid qualitative analysis (RQA), an established, pragmatic, team-based approach that quickly generates preliminary findings to inform real-time modifications and processes [55]. RQA involves (1) creating at least one neutral domain name (ie, topic) for each interview question; (2) creating a summary template with the domains to facilitate data condensation, in which the key data points are summarized; (3) testing the template for its utility and for establishing group process; (4) after verifying template utility and group process, completing a templated summary of each interview; (5) transferring summary points to a data matrix; and (6) conducting matrix analyses to assess the content of interview domains and any gaps in information and developing summaries of themes. Matrices will be developed for data from aims 1a and 1b and will be triangulated with regard to recommended revisions to the MMG protocol. Learnings from preresearch focus groups and the MST expert panel will be incorporated into intervention revisions and used to develop a comprehensive intervention description informed by the Template for Intervention Description and Replication (TIDieR) checklist [56].

### Aim 2: Pilot Trial

#### Overview

Using the revised protocol, we will conduct a pilot RCT of the MMG vs present-centered group therapy (PCGT; control condition) at an outpatient VAGLA mental health clinic (IM step 6). Over 24 months, male survivors of MST (n=32) will be randomized to the MMG or PCGT group (4 cohorts: 2 experimental and 2 control). We will investigate engagement (session attendance) as well as recovery-oriented outcomes (agency, hope, belongingness, and shame reduction) and psychological symptoms (PTSD, major depressive disorder, and suicidality) assessed before, immediately after, and 6 months after the intervention.

#### Participant Recruitment and Randomization

We will begin recruiting male survivors of MST through collaboration with VAGLA outpatient mental health clinics (ie, primary care, mental health clinics, trauma recovery services, substance use disorder clinics, and domiciliary services). During standard clinical care, health care professionals will inform male survivors of MST about the opportunity to participate in a study on men’s MST. These veterans will receive an informational study handout, which will also be publicly available. This handout will state that veterans will potentially receive financial compensation for baseline data collection. Interested veterans will be screened for eligibility and contact the study coordinator to provide written consent and arrange the collection of pretreatment data.

Individuals who do not meet the exclusion criteria (see below) will be randomly assigned to 1 of the 2 study groups: the MMG (n=8) or PCGT control (n=8). The process will be repeated for the second cohort. Participant randomization will be performed using a computer-generated randomization sequence prepared by an independent statistician, with allocation concealment maintained until assignment. Due to the nature of the intervention, participants cannot be blinded following treatment assignment. Because primary outcomes are patient reported, blinded outcome assessment is not feasible.

#### Data Management

All qualitative and quantitative data will be linked to a unique identification number assigned to each participant and entered into computerized files. Only the identification number will be linked to participant data in databases and paper documents. We will secure all paper records and electronic data files in compliance with current VA IRB policies. All data will be coded by the study coordinator. Datasets will be maintained for screening for out-of-range values and comparing a random sample of 10% of entered data to the original data collection forms. Problems or perceived errors with data entry will be addressed iteratively. Double entry procedures will be used on a select (10%) sample to assess for errors.

#### Eligibility Criteria

Eligible participants include any individual who identifies as a veteran cisgender man with a history of MST, speaks English, is aged 18 years or older, and is enrolled in VAGLA. Participants must (1) comprehend and sign the informed consent form, (2) report a history of MST, and (3) agree to complete the research instruments. Because this pilot trial is primarily designed to assess for feasibility, acceptability, and clinical signal, concomitant care (eg, psychiatric or individual and group therapy) will be permitted.

#### Exclusion Criteria

Veterans will be excluded if they demonstrate (1) severe suicidal ideation defined using the Columbia-Suicide Severity Rating Scale, chart-documented homicidal ideation, and behavioral flags per chart review; (2) severe and uncontrolled substance abuse (identified through chart review and discussion with health care professionals); (3) illness that inhibits engagement in study procedures (eg, inability to attend in-person visits); (4) inability to self-consent to participate; (5) completion of the MMG 5 or fewer years before; and (6) concurrent enrollment in a trauma-focused intervention. Through chart review, veterans who drop out of MMG or trauma-focused interventions after 3 sessions or less will still be eligible as this is considered early dropout. If immediate clinical attention is warranted, veterans will receive care via procedures outlined in the human participant protection plan.

#### Design

##### Overview

This pilot RCT will involve 12 weekly in-person sessions with an interventionist at the West Los Angeles Mental Health Clinic. The principal investigator (PI) will serve as the primary interventionist for the experimental condition during the first cycle, and a different staff psychologist will serve as the interventionist for the experimental condition during the second cycle. To distribute and minimize potential health care professional burden, 2 additional staff psychologists from Trauma Recovery Services Clinic (1 per cycle) will serve as interventionists for the control condition. All group sessions will be audio recorded for fidelity. Participant retention will be enhanced through financial compensation for trial participation. Participants will receive US $100 for completion of a pretreatment survey, US $50 for completion of the posttreatment survey, and US $50 for completion of the 6-month survey and interview.

While having the PI conduct the first experimental condition risks bias, this was strategically designed for three key reasons: (1) the PI developed the MMG treatment protocol and, thus, is most familiar with the approach; (2) it will allow for any needed protocol adjustments in preparation for training of another clinician for the second cohort; and (3) this will be a pilot RCT designed to assess appropriateness and feasibility for a future trial.

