##### MMG (Experimental Condition)

This is a 12-week group that meets for 90 minutes weekly. This group will draw on interventions developed in our pilot study (described above). The protocol will be further revised based on IM steps followed for aims 1 and 2.

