### Analysis

Following the CONSORT (Consolidated Standards of Reporting Trials) extension for randomized pilot and feasibility trials [63], the limited dataset will be underpowered to detect differences between conditions, and we did not design this pilot RCT to have power to examine or establish efficacy; rather, we are seeking to pilot the refined intervention to assess engagement outcomes, change in theorized targets, and initial clinical signals. Any missing data will be identified during analysis and noted in write-ups. We will use a linear mixed model for longitudinal data with a 2-level factor for group and a 3-level factor for time. The experimental and control groups will form the 2-level between-group factor, and the 3 time points (baseline, after treatment, and 6-month follow-up) will form the within-group factor.

To pretest the intervention, we will test the experimental vs control groups on exploratory data on clinically meaningful outcomes from baseline to after treatment. We hypothesize that participants assigned to the MMG will report improved engagement (session attendance) and comparable signs of recovery (agency, hope, belongingness, and shame reduction) and PTSD, depression, and suicidality measurements. This hypothesis will compare the impact of the MMG to that of PCGT at the posttreatment time point and 6-month follow-up (both as compared to baseline). Both comparisons will include psychometrically validated measures (RAS, EISS, GBS, PCL-5, and PHQ-9) and attendance.

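### The stated model pools two randomised cycles, between which both therapists and possibly the MMG protocol change, so it cannot show whether the two deliveries of MMG agree

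*Protocol article*

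**What the plan says.** All references are to the Protocol article.

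- **Size and structure (Aim 2, Overview).** "male survivors of MST (n=32) will be randomized to the MMG or PCGT group (4 cohorts: 2 experimental and 2 control").
- **Randomisation (Aim 2, Participant Recruitment and Randomization).** Eligible men are "randomly assigned to 1 of the 2 study groups: the MMG (n=8) or PCGT control (n=8"). Then: "The process will be repeated for the second cohort".
- **Therapists (Aim 2, Design, Overview).** The principal investigator (PI) "will serve as the primary interventionist for the experimental condition during the first cycle"; another staff psychologist takes over MMG in the second. Two further psychologists deliver PCGT, one per cycle.
- **Stability of the MMG protocol.** Aim 1, Overview: "we will convene a subset of aim 1a participants for an expert panel to finalize the MMG protocol". Aim 2, Design, Overview, gives as a reason for PI delivery in the first cycle that "it will allow for any needed protocol adjustments in preparation for training of another clinician for the second cohort". The section MMG (Experimental Condition) adds: "The protocol will be further revised based on IM steps followed for aims 1 and 2". Aim 2 is the trial itself.
- **Model (Aim 2, Analysis).** "We will use a linear mixed model for longitudinal data with a 2-level factor for group and a 3-level factor for time". No section names a cycle, cohort or therapist term, or promises results by cycle.

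**The concern.** Because 8 men are assigned to each arm within each cycle, cycle is a block of the randomisation. It also marks the point at which the MMG therapist changes from the developer to someone trained by the project, the PCGT therapist changes, and the MMG protocol may be adjusted. The stated model has no term for this block.

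The pilot is meant to give engagement results and initial clinical signals for a fully powered multisite trial, and such a trial would presumably need therapists other than the developer. If the two MMG deliveries perform differently, a single pooled figure hides it. This applies equally to attendance, the outcome on which MMG is hypothesised to do better.

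**Working it through.** **1. The plan's own figure.** 2 cycles × (8 MMG + 8 PCGT) = 32, as stated. Of the 16 MMG men, 8 (half) are treated by the PI.

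The plan gives no outcome SDs, correlations or cycle differences. The values below are assumptions, in units of the outcome SD.

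**2. Is the arm difference biased?** No, with balanced data. At 8:8 in each cycle, cycle is orthogonal to arm. In simulation (20,000 runs, cycle differences of 0 to 1.0 SD) the mean error of the arm difference was below 0.004 SD, with or without a cycle term. Unequal dropout could disturb this slightly. In a post-treatment comparison with MMG/PCGT completers of 7/5 in one cycle and 5/7 in the other, a 0.5 SD cycle difference shifts the arm difference by 0.5 × (7/12 − 5/12) = 0.08 SD.

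**3. Is precision lost on an outcome measured once, such as attendance?** Yes, modestly. If cycle means differ by δ, leaving cycle out multiplies the variance by 1 + δ²/4:

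| δ (SD) | Variance factor |
|---|---|
| 0.3 | 1.02 |
| 0.5 | 1.06 |
| 0.8 | 1.16 |

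Simulated standard errors agree: 0.361 without the term against 0.350 with it at δ = 0.5, and 0.379 against 0.350 at δ = 0.8.

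**4. Is precision lost on the change-from-baseline contrast?** This is what the plan says the mixed model will compare. I took 32 men, three time points, complete data, a random intercept, total SD 1 and within-person correlation ρ = 0.5. The standard error of the arm difference in change is √[2(1 − ρ)] × √(2/16) = 1 × 0.354 = 0.354.

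- Cycle difference of 0.8 SD, stable over time: it cancels from the change. Adding a cycle main effect altered the estimate by about 10⁻¹⁵ and left the standard error the same (0.359 with and without, 30 simulated datasets).
- Change from baseline differing by 0.8 SD between cycles: the standard error is about 0.37 with group and time only, and about 0.35 once cycle-by-time is added.

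For this contrast a cycle main effect alone does nothing with complete data. Only cycle-by-time can recover precision.

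**5. What does the pooled figure describe?** With equal cycle sizes it is the simple average of the two cycle-specific effects. Illustrations: (0.8 + 0)/2 = 0.4 SD; (1.0 + 0)/2 = 0.5 SD. Neither value describes either cycle.

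**6. Could the trial test whether the cycles agree?** No.

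- Each cycle compares 8 v 8, so the 95% half-width is t(0.975; 14) × √(2/8) = 2.145 × 0.5 = 1.07 SD.
- The difference between the two cycle-specific effects has standard error √(2/8 + 2/8) = 0.71 SD (simulated: 0.70).
- If the true effects were 1.0 and 0 SD, power to detect the difference would be about 27%.

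Results by cycle can therefore only be descriptive.

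**The case against.** The strongest reply has four parts.

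- **Little statistical harm.** This largely stands. Balanced allocation gives no bias. On a single-time-point outcome, omitting a real cycle difference makes the test conservative (simulated type I error 0.046 at 0.5 SD and 0.028 at 1.0 SD). A reader might infer that the omission distorts the arm difference, or that the 2–16% variance inflation applies throughout. The stated design and the change-from-baseline contrast do not support either.
- **Results by cycle cannot isolate the therapist.** This stands. The PCGT therapist changes too, so within each cycle arm is fully confounded with one therapist and one therapy group. It is tempting to read cycle 2 as the performance of MMG under non-developers, or the gap between cycles as the PI's effect. Neither follows. Nor does a cycle term deal with clustering within the four therapy groups.
- **The design is disclosed and iterative.** The article concedes that PI delivery risks bias, lists therapist effects as a limitation and disclaims efficacy. Finalising in aim 1 may mean only the version that enters the trial, and the revision drawn from aim 2 is not said to occur mid-trial. So a reader may not infer that the manual will change; the text says only that it may. But the provision for adjustment before the second cohort is explicit. The mitigation offered for therapist effects, fidelity monitoring and standard procedures, is weaker if the procedures may change when the therapist does.
- **Covariates belong in the analysis plan.** Partly fair: an unseen plan could add terms. But the article names the model's factors and omits the design's own randomisation block, and the status of the MMG protocol between cycles is not a matter for an analysis plan.

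**Conclusion.** The point holds as one of interpretation, with a modest gain in precision attached. The stated analysis pools a developer-led and a staff-led MMG, possibly in different versions, and does not show whether they agree. That limits what the pooled estimate can be said to represent.

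The size of any disagreement is unknown; the 0.8-versus-0 split is only an illustration. The precision cost is about 2–16% of variance on an outcome measured once, for assumed cycle differences of 0.3–0.8 SD. On the change contrast it is nil for a stable cycle difference, and a standard error of about 0.37 instead of 0.35 if change differs by 0.8 SD between cycles (ρ = 0.5, complete data).

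The documents do not support saying that the arm difference is biased, that the PI drives the result, or that this trial can establish how MMG performs under other therapists. For an underpowered pilot this is a moderate point, worth acting on because the remedy is nearly free and aim 2 recruitment has not begun.

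**What to change.** 1. **Model.** Include the randomisation cycle in the arm comparisons: cycle and cycle-by-time in the mixed model (3 degrees of freedom), and cycle in the attendance comparison (1 degree of freedom).
2. **Reporting.** Show the MMG–PCGT difference and attendance for each cycle with confidence intervals, labelled descriptive. State beside them that each cycle compares one MMG therapist with one PCGT therapist, and so can neither isolate the PI's effect nor establish performance under non-developers.
3. **MMG version.** Reconcile the Aim 1 Overview, where the protocol is finalised, with Aim 2, Design, Overview and MMG (Experimental Condition), which leave it open to adjustment. Record the version used in each cycle. If it changed, do not describe the pooled estimate as the effect of one protocol.

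The cost is a few lines of analysis text, one small table and a version log. No extra participants or measurements are needed.
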